## Abstract

**Background:**

Consumption of nuts improves cardio-metabolic risk factors in clinical trials and relates to lower risk of cardiovascular disease (CVD) in prospective observational studies. However, there has not been an adequately powered randomized controlled trial to test if nuts supplementation actually reduces incident CVD. In order to establish the feasibility of such a trial, the current study aimed to assess the acceptability and adherence to long-term nut supplementation amongst individuals at high CVD risk in China.

**Methods:**

This protocol described a 6-month trial performed in Ningxia Province in China among participants with a history of CVD or older age (female ≥65 years, male ≥60 years) with multiple CVD risk factors. Participants were randomized to control (received non-edible gift), low dose walnut (30 g/d), or high dose walnut (60 g/d) groups in a 1:1:1 ratio. Walnuts were provided at no cost to participants and could be consumed according to personal preferences. Follow-up visits were scheduled at 2 weeks, 3 months and 6 months. The primary outcome was fasting plasma alpha linolenic acid (ALA) levels used as an indicator of walnut consumption. Secondary outcomes included self-reported walnut intake from the 24 h dietary recalls. The target sample size of 210 provided 90% statistical power with two-sided alpha of 0.05 to detect a mean difference of 0.12% (as percent of total fatty acid) in plasma ALA between randomized groups.

**Results:**

Two hundred and ten participants were recruited and randomized during October 2019. Mean age of participants was 65 years (SD = 7.3), 47% were females, and 94% had a history of CVD at baseline. Across the three study groups, participants had similar baseline demographic and clinical characteristics.

**Discussion:**

This trial will quantify acceptability and adherence to long-term walnut supplementation in a Chinese population at high risk of CVD. The findings will support the design of a future large trial to test the effect of walnut supplementation for CVD prevention.

**Trial registration:**

NCT04037943

**Protocol version:** v3.0 August 14 2019

**Supplementary Information:**

The online version contains supplementary material available at 10.1186/s12937-020-00660-7.

## Background

Tree nuts (referred to hereafter as nuts) such as walnuts, almonds, and pistachios are rich in unsaturated fats, soluble fibre, phytosterols, and antioxidants. In meta-analyses of short-term randomized controlled trials (RCT), increased intake of nuts improves cardiovascular disease (CVD) risk factors such as total cholesterol, LDL cholesterol, apolipoprotein B, and triglycerides, as well as markers of endothelial function and glycemic control [1–3]. Unsaturated fats – about 50% of total fats in most nuts – also significantly improve glycemic control in RCTs [4, 5]. These effects appear dependent on the amount (dose) rather than the types of nuts, although most studies to date have focused on walnuts and almonds [1]. Prospective observational studies also support a beneficial role of nuts for the prevention of CVD. A recent meta-analysis has found that higher nuts intake is associated with lower risk of incident CVD, with about 20% lower risk per daily 1-oz (28 g) serving (RR: 0.79, 95% CI: 0.70, 0.88) [6].

While the findings from short-term trials and prospective cohorts suggest likely metabolic benefits and protection against CVD, and a growing number of dietary guidelines around the world recommend the incorporation of nuts as part of a healthy dietary pattern [7–9], several key questions remain unresolved. First, no long-term RCTs have tested the effects of nuts consumption on the risk of CVD. The PREDIMED study, a RCT among Spanish adults, has found that advice to consume a Mediterranean diet supplemented with mixed nuts (30 g/day) significantly reduced incident CVD, compared to advice to follow a low-fat diet [10]. However, the design of PREDIMED does not allow separation of the effects of nuts alone, vs. the Mediterranean dietary advice as a whole. In addition, errors and inconsistencies in the randomization process of PREDIMED, have raised controversy over its findings [11]. Crucially, nearly all the prior trials and cohort studies, including the PREDIMED trial, have been performed in high-income Western populations. The effects of increased nuts intake on CVD in lower- and middle-income countries remain uncertain. For instance, only three controlled trials have been conducted in Chinese participants (2 in China, 1 in Taiwan) [12–14], with several additional trials in other Asian populations [15, 16]. Their findings support likely benefits of nuts supplementation in reducing LDL cholesterol and improving other CVD risk factors. However, all of the trials were short-term (less than 3 months) and not able to test for clinical CVD events.

Cardiovascular disease is the leading cause of death and disability in China [17]. Large dietary surveys indicate that low levels of nuts consumption could be a significant contributor to CVD burden in China, with estimated mean nuts intake of only 5.4 g/day across diverse geographical regions [18]. An appropriately designed and powered RCT to test the effect of nuts supplementation on the risk of incident CVD events in China is therefore of significant scientific and public health importance. We hereby report the protocol for a 6-month walnut supplementation trial in a rural area of China with high rates of CVD, to obtain data on feasibility of long-term walnut supplementation to support and help to refine the design of a future long-term large RCT testing the effect of nuts supplementation on CVD risk. The main objectives of the current trial are to assess the acceptability and adherence to two different doses of walnut supplementation (30 and 60 g per day). The exploratory objectives are to determine the effects of walnut supplementation on cardiovascular risk factors including blood lipids, fasting glucose, and body weight.

## Methods

### Study design

The ‘Nuts for the prevention of cardiovascular disease in Chinese adults’ (NUTS) study was a randomized, controlled, single blind (blinded investigators and blinded assessments of all study endpoints), three-group parallel design trial lasting for 6 months.

Participants were randomized to one of the three groups in a 1:1:1 ratio: control (non-edible gift), low dose (30 g/day) walnut intervention group, and high dose (60 g/day) walnut intervention group (Fig. 1). Written informed consent was obtained from each study participant.

**Fig. 1 Fig1:**
[figure not shown]
Trial Flowchart. 210 participants with high risk of CVD were recruited from 6 rural villages in Ningxia Province, China. They were randomized in a 1:1:1 ratio to either the control group, or low-dose walnut (30 g/day) intervention group, or high-dose walnut (60 g/day) intervention group; and followed-up for 6 months. Outcome data were collected from participants at study baseline, the interim visits, and at the end of trial visit

### Study population

We have chosen Ningxia to conduct this trial, since it is a province with high prevalence and mortality rate of stroke and ischemic heart disease [19–21] and the project team has established collaborations with local academic and government institutions. Following consultation with these partners, we recruited adults from six rural villages near Qingtongxia City in Ningxia, based on their willingness to participate and their geographic accessibility. Suitable villages needed to have at least one village doctor who was able to facilitate primary screening of participants.

In each village, we recruited individuals at high risk of CVD based upon having a history of CVD or a high risk of CVD. Inclusion criteria were a history of CVD (defined by prior hospitalization for a myocardial infarction or stroke, unstable angina, coronary artery bypass graft surgery, percutaneous coronary intervention, peripheral revascularization, symptomatic with documented hemodynamically-significant carotid or peripheral vascular disease, or amputation secondary to vascular disease); or older age (≥60 for males, ≥65 years for females), plus at least two of the following CVD risk factors: 1) type 2 diabetes including treatment with at least two oral anti-hyperglycaemic agents, or insulin, 2) systolic blood pressure ≥ 140 mmHg while on one or more antihypertensive agents, 3) current daily smoking, 4) dyslipidaemia defined as HDL-cholesterol < 1.0 mmol/L or LDL-cholesterol > 6.0 mmol/L, or 5) micro- or macro-albuminuria. The definition of high risk individuals was selected to ensure adequate numbers of events and statistical power in the future planned large-scale trial to test walnut supplementation to reduce CVD events. Data from completed and ongoing large-scale trials indicated that patients meeting these criteria experienced an annual event rate of 3.5% for the occurrence of major adverse cardiovascular events [22, 23].

Screening of CVD risk factors was based on self-report with support of physical evidence. Participants were deemed to have the relevant risk factors if they were able to present evidence from a laboratory measurement, prescription drug packaging, tobacco packaging, or clinical report within the past 12 months.

Individuals were excluded if they had never or rarely consumed any types of nuts, had self-reported allergy to nuts (i.e. history of food allergy with hypersensitivity to any of the components of nuts), had other serious medical conditions that prevent nuts consumption (e.g. digestive disease with fat intolerance), had any medical condition thought to limit survival to less than 1 year, had difficulty with consuming nuts (e.g. dental health issues that prevent chewing walnuts), or were unwilling to consume nuts.

### Recruitment and consent

Village doctors distributed study information sheets in their villages and registered individuals who were interested to participate 2 weeks before study recruitment. Potential participants were invited by the village doctors to attend the screening interview at the village clinics. At the screening interview, potential participants were interviewed by trained study staff who explained the background, objectives, and procedures of the trial, sought and obtained written informed consent, confirmed eligibility, and completed the baseline survey. Participants who provided informed consent were invited to complete the baseline fasting blood sample collection the next day. Only one eligible participant was recruited from each household to avoid potential contamination across randomized groups.

### Randomization

Randomization was done centrally by an independent biostatistician using a computer-generated random number sequence after the completion of the baseline survey. Participants were randomized with stratification by village in a 1:1:1 allocation ratio to either one of the intervention groups or to the control group.

### Rationale for the chosen walnut intervention

Walnuts contain a high amount of protein, dietary fibre, vitamins, minerals and phytosterols [24]. Walnuts are a rich source of both omega-6 and omega-3 polyunsaturated fatty acids (linoleic and alpha linolenic acid [ALA]) [25] and improve cardio-metabolic risk factors in short-term clinical feeding trials including lowering LDL-cholesterol [26, 27]. Walnuts have made up the largest proportion (50%) of the mixed nuts used in the PREDIMED study [10]. In addition, walnuts are relatively soft compared to other nut types, making them easier to be chewed and consumed by those with oral health issues such as older adults, who are likely to make up a significant proportion of those recruited to the trial. Walnuts are also readily accessible since China grows a large volume of walnuts [28]. Commercially-available roasted, unsalted walnuts were used in the trial for enhanced taste and longer shelf life. The study walnuts contained 4.47 g of protein, 17.64 g of total fat, 5.73 g of carbohydrate and total energy of 811KJ per 30 g.

A dose-response relationship between greater nuts intake and lower cardio-metabolic risk has been generally observed across a range of nuts intake between 5 g to 100 g per day, with stronger effects for trials providing ≥60 g/day [1, 2]. Since the effect of walnut intake on CVD risk is likely mediated by changes in cardio-metabolic risk factors, we seek to evaluate if a higher dose of daily walnut supplementation is as acceptable as a lower dose. Therefore, for this trial, we tested both 30 g per day (corresponding to many current dietary recommendations), as well as a higher dose of 60 g per day of walnut supplementation.

### Intervention and control

Participants in the intervention groups were provided sachets containing 30 g of roasted and unsalted walnuts free of charge. For the 30 g/day arm, 1 sachet/day was provided, and for the 60 g/day arm, 2 sachets/day were provided. The walnuts were purchased from a local food manufacturer who sourced walnuts from Chinese walnut growers and packaged them in accordance with Chinese food standards (GB/T 20398–2006). The participants were instructed to open and consume the allocated dose of walnuts at any time of the day according to their personal preference, but not to share the walnuts with family members. To ensure freshness, participants were provided with sufficient sachets for the first 3 months of the intervention at baseline and were provided with the remainder at the 3-month follow-up study visit.

Participants in the control group continued with their usual diet without introduction of any nuts supplement. They were provided with small, inedible toiletry gifts at baseline and were provided with similar gifts at each follow-up visit to ensure equal study contacts across all the study groups and encourage attendance at the follow-up visits.

### Data collection and follow up

Informed consent was obtained from each participant before any data collection (Table 1). At baseline, eligible participants completed an interviewer-administered questionnaire, a validated 95-item food frequency questionnaire (FFQ) that asked participants about their usual dietary pattern over the past 12 months, and a 24-h dietary recall [29]. Each participant also underwent physical examination to record height, weight, waist and hip circumferences (Inbody-370S scale and measuring tapes, and anthropometry assessment conducted according to the International Society for the Advancement of Kinanthropometry (ISAK) protocols), and blood pressure (OMRON-7124). After an overnight fast, participants had their blood samples collected at the local township hospital by trained nurses. One blood sample was drawn into 5 ml EDTA-anticoagulated vacutainer tube, and used for measurement of blood lipids (total triglycerides, total cholesterol, LDL-C, and HDL-C) at the township hospital laboratory immediately following routine procedures for the results to be provided to the participants. Another blood samples were drawn into 5 ml EDTA-anticoagulated vacutainer tubes and immediately separated, aliquoted, and stored at − 30 °C in freezers at the township hospital before being couriered (at − 30 °C) to the Ningxia Medical University central laboratory within 72 h of blood collection. All plasma samples were subsequently stored at − 80 °C in the central laboratory. Blood samples will be tested for plasma alpha-linolenic acid (ALA), glucose, LDL-cholesterol, HDL-cholesterol, total cholesterol, and total triglyceride levels. All the specimens will be disposed of 12 months after the end of trial.

**Table 1 Tab1:** Timeline for key events and collection of outcome data for the NUTS trial

			Follow up 24 weeks				
			Baseline				
Week	−2	−1	0	1	2	12	25^a^
Months			0			3	6
*Pre-intervention screening*							
Information sheets distribution	╳						
Consent for pre-screening	╳	╳					
Pre-screening	╳	╳					
*Baseline*							
Informed consent			╳				
Assessed for eligibility			╳				
Demographics			╳				
Disease history			╳				
Medication use			╳				
Food Frequency Questionnaire			╳				
*Intervention*							
Randomization				╳			
Dispense walnuts (intervention groups)				╳		╳	
Dispense non-edible gifts (control group)				╳	╳	╳	╳
*Endpoint collection*							
Blood pressure			╳				╳
Fasting blood			╳				╳
Anthropometric measurements^b^			╳				╳
24-h dietary recall			╳				╳
Adherence and acceptability (intervention groups)					╳	╳	╳

^a^ 25 week or early withdrawal; ^b^ Weight, height, waist and hip circumference measurements

Interim visits occurred at 2 weeks and 3 months after the baseline for each participant. Blood test results describing blood lipids were provided to participants at the 2-week study visit, with referral to local physicians for management if blood lipid levels exceeded clinical guidelines. Participants in the intervention groups were reminded to consume walnuts every day and completed a 7-item follow-up questionnaire (Supplementary material) related to acceptability and adherence to the walnut supplementation at both interim visits. Participants in the control group did not answer this questionnaire, but received non-edible gifts at each interim visit. At the end of trial (6 months after randomization), all participants completed the same 24-h dietary recall as they did at baseline to assess the change in nuts intake, and fasting blood samples were collected according to the same procedure as at baseline. At the end of the trial, participants from intervention groups again answered the 7-item questionnaire regarding the acceptability and adherence to walnut supplement, and the control group received a non-edible gift (Table 1). All the participants will be notified of the study results once the trial has been completed.

Any condition which required hospitalization was collected at each follow-up visit as adverse event. All adverse events were listed and reported to the ethics committees periodically. Participants who developed food allergy with hypersensitivity to any of the components of walnut in the intervention groups were referred to and had the allergy confirmed by a doctor. Intervention was discontinued among those participants but they were followed up until the end of the trial.

Study personnels were divided into an intervention delivery group (who were not blinded to the allocation of treatment) and an outcome assessment group (who were blinded to the allocation of treatment). The intervention delivery group delivered the walnuts and non-edible gifts and performed the interim study visit questionnaires related to acceptability and adherence. The outcome assessors administered the FFQ, anthropometric assessments, and 24-h dietary recall and collected blood samples from participants at baseline and at the end of trial.

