### Statistical analysis

Differences in between group post-treatment mean plasma ALA will be assessed by linear regression. In the primary analyses, study group assignment will be treated in the ANCOVA model as a categorical independent variable, with the control as the reference group. There will be three pair-wise comparisons: 1) 30 g/day walnut group vs. control, 2) 60 g/day walnut group vs. control, 3) 60 g/day walnut group vs. 30 g/day walnut group. Analyses will adjust for baseline plasma ALA and villages, and follow the intention-to-treat principle. An additional sensitivity analysis will be performed stratified by the baseline CVD status to examine any potential effect modification on the primary outcome.

For the secondary outcome of self-reported mean walnut intake (g/day) assessed by 24-h diet recalls, and the exploratory outcomes (plasma CVD lipids risk factors), differences in end of trial mean values between groups will be assessed by linear regression following the same approach as for the primary outcome.

Self-reported consumption patterns and satisfaction related to walnut intake will be assessed by the 7-item short questionnaire. The questionnaire included the following items: whether the participants consumed the walnuts, the ways they consumed the walnuts, and the number of times of walnuts intake in a day (each will be summarized as frequencies and %); as well as the number of days per week the participants consumed walnuts and their satisfaction rating on walnut flavour (will be summarized as mean ± SD).

Statistical significance is defined as two tailed α = 0.05.

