### Participant characteristics

Participant recruitment started on October 16, 2019 and was completed on October 22, 2019. A total of 246 individuals were screened, and 210 met eligibility criteria and provided informed consent to participate in the trial. Ninety-four percent of participants were recruited on the basis of a history of CVD. Baseline characteristics of the participants were shown in Table 2. The participants were older adults (mean [SD] age = 65 ± 7 years) and approximately half were female (47%). Most participants attained up to primary school education (73%), with about 60% of participants were either past or current smokers. Only a small proportion were current drinkers (4.3%). Most participants had a history of ischemic heart disease (81%), and many also had a history of stroke (31%). Participants had similar baseline demographic and medical characteristics across the three randomized groups.

**Table 2 Tab2:** Baseline characteristics of trial participants

	Total (*n* = 210)	Control (*n* = 70)	Low dose (*n* = 70)	High dose (*n* = 70)
Age (y), mean (SD)	65.4 (7.3)	64.4 (7.4)	64.7 (8.5)	67.0 (5.7)
Female (%)	46.7	47.1	50.0	42.9
Education				
Primary school or lower (%)	73.3	70.0	70.0	80.0
Junior high school (%)	18.1	17.1	18.6	18.6
Senior high school or above (%)	8.6	12.9	11.3	1.4
Past smoker (%)	44.3	44.3	40.0	48.6
Current smoker(%)	15.2	17.1	11.4	17.1
Past drinking (%)	34.3	35.7	34.3	32.9
Current drinking (%)	4.3	2.9	2.9	7.1
Body mass index (kg/m^2^), mean (SD)	26.4 (3.4)	26.5 (3.4)	25.8 (3.6)	26.3 (3.1)
Body weight (kg), mean (SD)	68.0 (11.1)	69.1 (11.6)	67.8 (12.5)	67.0 (9.0)
Waist hip ratio (SD)	0.94 (0.1)	0.96 (0.06)	0.94 (0.06)	0.93 (0.06)
Male (SD)	0.95 (0.1)	0.97 (0.07)	0.93 (0.06)	0.93 (0.06)
Female (SD)	0.93 (0.1)	0.93 (0.06)	0.94 (0.06)	0.93 (0.06)
Systolic blood pressure (mm Hg), mean (SD)	147.1 (19.9)	146.5 (19.9)	146.5 (21.8)	146.8 (18.1)
Diastolic blood pressure (mm Hg), mean (SD)	84.9 (12.0)	85.0 (12.9)	85.0 (12.3)	84.8 (10.9)
Medication use				
Lipid lowering agent (%)	67.1	55.7	78.6	67.1
Blood pressure lowering agent (%)	85.2	84.3	80.0	91.4
Disease history				
CVD^a^(%)	95.2	92.9	98.6	94.3
Stroke (%)	31.0	24.3	25.7	42.9
Transient ischemic attack (%)	29.5	21.4	21.4	45.7
Ischemic heart disease (%)	81.0	78.6	90.0	74.3
Congestive heart failure (%)	10.5	8.6	8.6	14.3
Peripheral arterial disease (%)	7.6	8.6	5.7	8.6
Hypertension (%)	83.3	81.4	80.0	88.6
Diabetes mellitus (%)	31.4	34.3	30.0	30.0

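### The exploratory lipid comparisons, mainly 30 g against control, may be distorted in either direction because baseline lipid-lowering use differs by chance, is not in the model, and is scheduled for recording only at baseline

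*Protocol article*

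**What the plan says.** All references are to the protocol article.

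- **Data collection and follow up.** "Blood test results describing blood lipids were provided to participants at the 2-week study visit, with referral to local physicians for management". The referral is conditional: "if blood lipid levels exceeded clinical guidelines". No arm is treated differently. Table 1 places randomization at week 1, so this feedback follows allocation.
- **Table 1.** The row "Medication use" has a cross at week 0 and nowhere else.
- **Statistical analysis.** For the primary outcome: "Analyses will adjust for baseline plasma ALA and villages, and follow the intention-to-treat principle". For the lipid outcomes: "differences in end of trial mean values between groups will be assessed by linear regression following the same approach as for the primary outcome". I read this as each lipid's own baseline value plus village.
- **Randomization.** Village is the only stratification factor.
- **Table 2** (columns total, control, low dose, high dose): "Lipid lowering agent (%) 67.1 55.7 78.6 67.1".
- **Participant characteristics.** "Participants had similar baseline demographic and medical characteristics across the three randomized groups". The Results paragraph of the Abstract makes the same claim.
- **Study outcomes.** Plasma ALA is primary. Plasma lipids are exploratory.

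**The concern.** The trial's own procedure can prompt lipid treatment after randomization, and lipids at six months are then compared between arms. The arms did not enter with the same scope for new treatment: 31 of 70 controls were not on a lipid-lowering agent, against 15 of 70 in the low-dose arm.

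Two mechanisms follow, and they pull in opposite directions:

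- New treatment among the untreated would be more frequent in controls. It would lower control lipids and hide a walnut benefit.
- Participants already on treatment probably have lower usual lipids. A single baseline measurement captures this only in part, because of within-person variation, so the arm with more treated participants (low dose) would look better than it should.

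The planned model has no term for either mechanism, and the published schedule shows no record of drug changes during follow-up.

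The effect on blood lipids is a stated exploratory objective (Background). The rationale for the intervention supposes that any CVD effect runs largely through cardio-metabolic risk factors. The Discussion cites LDL-cholesterol reduction when defending the population for a future trial of more than 20,000. A distorted lipid estimate could therefore carry into that design. Separately, the statement that the groups were similar does not fit Table 2.

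**Working it through.** **1. Reproduce Table 2 (70 per arm).** On a lipid-lowering agent: 39/70 = 55.7%, 55/70 = 78.6%, 47/70 = 67.1%; total 141/210 = 67.1%. All four published figures reproduce. Not on an agent: 31/70 = 44.3%, 15/70 = 21.4%, 23/70 = 32.9%.

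**2. Size of the imbalance.** Expected counts per arm are 141/3 = 47 treated and 23 untreated. The deviations are −8, +8 and 0.

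Chi-square = (64 + 64)/47 + (64 + 64)/23 = 2.72 + 5.57 = 8.29 on 2 df, p = 0.016.

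| Pair | Chi-square p | Fisher p |
|---|---|---|
| Control vs low dose | 0.004 | 0.007 |
| Control vs high dose | 0.16 | 0.22 |
| Low vs high dose | 0.13 | 0.18 |

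Only control against low dose stands out. The p-values describe how uneven this draw was; they do not test the randomization.

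**3. Other rows behind the similarity statement.** Transient ischemic attack 15/15/32 of 70 (21.4/21.4/45.7%): chi-square 13.2, p = 0.001. Stroke 17/18/30 of 70 (24.3/25.7/42.9%): chi-square 7.0, p = 0.03.

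**4. First mechanism alone, as a crude difference.** Bias = (difference in share untreated) × (share who start) × (LDL fall on starting). The documents give neither of the last two. Assume 10% to 50% start and a fall of 0.5 to 1.5 mmol/L:

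- Low dose minus control: (0.443 − 0.214) × 0.10 × 0.5 = +0.01, up to 0.229 × 0.50 × 1.5 = +0.17 mmol/L.
- High dose minus control: 0.114 × 0.10 × 0.5 = +0.01, up to 0.114 × 0.50 × 1.5 = +0.09 mmol/L.

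This ignores the baseline covariate, the lipid-level trigger for referral and the second mechanism, so it is not an estimate for the planned analysis.

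**5. The planned type of model, both mechanisms.** Simulated ANCOVA for low dose vs control, 70 per arm, the observed medication split, no walnut effect, 1,500 runs per setting. Assumed values, none from the documents: untreated mean LDL 2.8 mmol/L, SD 0.8, slope of final on baseline value 0.6, starts only in untreated participants with LDL above 2.6, and a fall of 1.0 on starting. Village was left out for simplicity. B is the assumed LDL lowering already present in treated participants.

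| Share of eligible who start | B (mmol/L) | Difference, baseline-adjusted | Type I error | Difference, adding baseline drug use | Type I error |
|---|---|---|---|---|---|
| 0 | 0 | −0.001 | 5.3% | 0.000 | 5.1% |
| 0 | 0.5 | −0.045 | 6.5% | −0.002 | 4.8% |
| 25% | 0 | +0.033 | 6.8% | −0.001 | 5.9% |
| 25% | 0.5 | −0.010 | 4.7% | +0.004 | 4.5% |
| 50% | 0 | +0.065 | 7.8% | −0.004 | 4.9% |
| 50% | 0.5 | +0.010 | 5.9% | −0.003 | 4.9% |

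A hand check of the most negative row: −0.5 × 0.229 × (1 − 0.6) = −0.046, in line with −0.045.

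The Monte Carlo standard error of a 5% rate is √(0.05 × 0.95/1500) = 0.6 percentage points. So 7.8% is a real excess, while 4.5% to 5.9% is compatible with 5%.

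When medication was instead drawn at random at 67.1% in both arms, the baseline-adjusted differences lay between −0.002 and +0.004. The problem is tied to this imbalance and not to the design on average.

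**The case against.** **Allocation was random and one referral rule covers every arm.** This stands. The imbalance is chance, and over repeated randomizations the intention-to-treat contrast is valid as an effect alongside usual lipid care. A reader might infer that the lipid outcomes are confounded; that goes too far. What remains is distortion conditional on the imbalance that occurred.

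**Referral depends on the lipid level, and the baseline level is already a covariate.** This is partly right, and it rules out taking the crude figures in step 4 as the bias. It does not remove the problem: the simulation includes both the trigger and the baseline covariate and still leaves up to 0.065 mmol/L, because the level does not tell the model who was untreated.

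**Table 1 may be incomplete.** It marks the food frequency questionnaire at baseline only, while the text has assessors administering it at the end of the trial as well, and it has no row for hospitalizations. The article also condenses a full protocol that is not shown. This stands against any claim that drug changes were certainly not captured. It does not answer the points the article does state: the model, the published schedule and the similarity statement.

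**Adding a covariate because a baseline test is significant is poor practice, and the prespecified model is no error.** Agreed. The reason to add it is its expected relation to lipid levels, and it can sit beside the prespecified model.

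**Only exploratory outcomes are touched, and the quoted contrast is the most extreme pair.** Both stand and limit the weight of the point.

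**Conclusion.** The point holds in limited form. The exploratory lipid comparisons, chiefly 30 g against control, are at risk of distortion given a chance imbalance in baseline lipid-lowering use of 22.9 percentage points (78.6% vs 55.7%). The high-dose contrast with control is weaker, at 11.4 points.

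A reader might infer a one-way bias toward no benefit. With 25% to 50% of the untreated starting and an LDL fall of 0.8 to 1.2 mmol/L, the crude formula gives 0.229 × 0.25 × 0.8 = 0.05 to 0.229 × 0.50 × 1.2 = 0.14 mmol/L. The documents do not support that. They give no start rate, no LDL response and no lipid SD, and under the planned type of model the simulated difference spans zero (−0.045 to +0.065 mmol/L, type I error 4.7% to 7.8%). Those figures rest wholly on the assumed values and show plausibility, not size. In every setting simulated, adding baseline drug use brought the difference to within 0.004 of zero.

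The primary ALA outcome and its power are not affected. The similarity statement conflicts with Table 2 whatever one concludes about bias.

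**What to change.** 1. Before unblinding, specify an analysis of the lipid outcomes that adds baseline lipid-lowering use as a covariate, at minimum as a sensitivity analysis beside the prespecified model. The variable is already collected.
2. Record lipid-lowering drug use at the end-of-trial visit in all three arms, retrospectively if that visit has passed, and report starts and stops by arm. If the full protocol already collects this, say so and correct Table 1.
3. In the Abstract (Results) and in Participant characteristics, replace the statement that the groups were similar with one that names the imbalances in lipid-lowering use (55.7/78.6/67.1%), stroke (24.3/25.7/42.9%) and transient ischemic attack (21.4/21.4/45.7%).

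The cost is one covariate, one question and slightly less favourable text. Retrospective recall of drug changes would be less reliable than a record made at the visit. Nothing here alters the return of results, the referral or any treatment.
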